**LIST OF ABBREVIATIONS AND RELEVANT DEFINITIONS**

|         |                                                                                                                                                                                                                                                                                                                                           |
|---------|-------------------------------------------------------------------------------------------------------------------------------------------------------------------------------------------------------------------------------------------------------------------------------------------------------------------------------------------|
| ABR     | ABR form (General Assessment and Registration form) is the application form that is required for submission to the accredited Ethics Committee (ABR = Algemene Beoordeling en Registratie)                                                                                                                                                |
| AE      | Adverse Event                                                                                                                                                                                                                                                                                                                             |
| AR      | Adverse Reaction                                                                                                                                                                                                                                                                                                                          |
| CA      | Competent Authority                                                                                                                                                                                                                                                                                                                       |
| CCMO    | Central Committee on Research Involving Human Subjects                                                                                                                                                                                                                                                                                    |
| CV      | Curriculum Vitae                                                                                                                                                                                                                                                                                                                          |
| DSMB    | Data Safety Monitoring Board                                                                                                                                                                                                                                                                                                              |
| EU      | European Union                                                                                                                                                                                                                                                                                                                            |
| EudraCT | European drug regulatory affairs Clinical Trials GCP Good Clinical Practice                                                                                                                                                                                                                                                               |
| IB      | Investigator's Brochure                                                                                                                                                                                                                                                                                                                   |
| IC      | Informed Consent                                                                                                                                                                                                                                                                                                                          |
| IMP     | Investigational Medicinal Product                                                                                                                                                                                                                                                                                                         |
| IMPD    | Investigational Medicinal Product Dossier                                                                                                                                                                                                                                                                                                 |
| METC    | Medical research ethics committee (MREC); in Dutch: medisch ethische toetsing commissie (METC)                                                                                                                                                                                                                                            |
| (S)AE   | Serious Adverse Event                                                                                                                                                                                                                                                                                                                     |
| SPC     | Summary of Product Characteristics (in Dutch: officiële productinformatie IB1-tekst)                                                                                                                                                                                                                                                      |
| Sponsor | The sponsor is the party that commissions the organisation or performance of the research, for example a pharmaceutical company, academic hospital, scientific organisation or investigator. A party that provides funding for a study but does not commission it is not regarded as the sponsor, but referred to as a subsidising party. |
| SUSAR   | Suspected Unexpected Serious Adverse Reaction                                                                                                                                                                                                                                                                                             |
| Wbp     | Personal Data Protection Act (in Dutch: Wet Bescherming Persoonsgegevens)                                                                                                                                                                                                                                                                 |
| WMO     | Medical Research Involving Human Subjects Act (Wet Medisch-wetenschappelijk Onderzoek met Mensen)                                                                                                                                                                                                                                         |

## SUMMARY

**Rationale:** The experience of positive emotions reduces daily life stress-sensitivity, an endophenotype for depression, but also attenuates the expression of genetic risk for depression. This research proposal, therefore, will focus on the changeability (plasticity) of the ability to experience positive emotions in response to daily life events (natural rewards), as a first step towards novel (preventive) interventions in depression

**Objective:**

- 1) Can the ability to experience reward in daily life be experimentally modified?
- 2) How does experimental modification of reward impact on depressive symptomatology and can individual variation be traced to genetic variation.

**Study design:** An intervention study is used in which subjects are randomized to treatment as usual (TAU) or TAU + mindfulness-based cognitive therapy. Experience Sampling Method (ESM) is a structured diary, momentary assessment technique to study subjects in their daily life. Before and after the intervention subjects undergo a six-day period of ESM assessment. Subjects will be globally informed, but remain blind as to how ESM measures relate to testing the hypothesis.

**Study population:** A sample of 120 depression-remitted adult subjects with residual symptomatology (Ham-17>7) recruited from the community mental health centre in Maastricht (CMHC).

**Intervention (if applicable):** The experimental group receives 8 weeks of mindfulness training by an experienced trainer in addition to their normal treatment, if any. Sessions are weekly (2,5 hours a session) and subjects receive daily homework exercises. The control group continues their normal treatment, if any.

**Main study parameters/endpoints:** The increase in reward experience in daily life, whereby reward experience is conceptualised as the effect of small daily life positive events on positive mood state. Since ESM measurements are performed 10 times a day for 6 days, there will be a maximum of 60 measurements within each subject concerning effects of positive events on positive mood state in the flow of daily life.

**Nature and extent of the burden and risks associated with participation, benefit and group relatedness:** There are no health risks associated with participation. There is a personal benefit for subjects in that they are randomized to receive an extra training that is expected to improve their resilience against depression. Time investment for subjects is 2,5 hours for questionnaires (distributed over three meetings, including the screening). In addition, they participate twice in the ESM protocol (6-day period of filling in dairies concerning daily life events and mood). Before the start each ESM protocol they have to come for a short meeting (15 -30 min) to receive specific instructions related to this

procedure. Of course the subjects (in the experimental condition) also have to participate in the MBCT training and invest time there.

## 1 INTRODUCTION AND RATIONALE

The bulk of depression research is on negative mood states with little attention to positive emotions. Positive affect (PA) and negative affect (NA) are not two extremes within a unidimensional construct, but relatively independent, and there is evidence that the capacity to experience positive emotions may have strong protective effects against depression. According to the “broaden and build” theory, the experience of positive emotions at times of stress reduces the likelihood of developing negative mood outcomes. The reason for this is, first, that positive emotions like joy, interest, contentment and love stimulate exploration of the environment and interaction with others, thus increasing the subjects’ physical and social resources. Second, positive emotions, in contrast to their negative counterparts, increase the attentional focus, which helps people make use of the positive elements, or natural rewards, present in the environment at times of stress, as opposed to narrowing the attentional focus to the negative component of the situation. The process of attentional broadening thus likely prevents people falling into a spiral of negative thinking.

### *My previous work leading to the proposal*

In a twin study (n=279 twin pairs), I identified a depression endophenotype of negative mood states (Y-axis figures below) in response to minor stressors (X-axis figures below) measured in the flow of daily life (this negative mood response to minor stressors is hereafter referred to as “negative affective reactivity”; figure left). In the same twin sample, I tested the hypothesis that experience of positive emotions at the time of the stressor decreases negative affective reactivity. The data confirmed this hypothesis: PA protected subjects from developing negative mood states in response to daily life minor stressors (figure right). In addition, PA at the time of the momentary stress experience also attenuated the association between genetic risk for depression (expressed as co-twin depression status) and negative affective reactivity. The experience of PA may thus be of prime importance in mitigating both symptoms of, and expression of genetic risk for, depression.

[figure not shown]

In order to establish possible clinical relevance of these findings, it becomes necessary to i) quantify the extent to which people are able to use natural rewards in the environment in order to generate PA, and ii) establish whether this ability can be learned. To this end I operationalised, using the Experience Sampling Method (ESM; see below), the ability to

experience positive emotions from everyday life situations as the *effect of minor events on positive affect in the flow of daily life* (hereafter: reward experience).

I hypothesize that learning to experience positive emotions from daily events is i) possible and ii) may protect against (risk for) depression, examining i) the degree of plasticity of the ability to experience reward (can it be learned), ii) its impact on residual depression and iii) genetic associations with the brain reward system.

#### *The brain reward system*

Depressed subjects have impaired reward function (anhedonia or inability to experience reward). The brain reward system involves structures of the mesocorticolimbic system, with dopamine pathways originating in the ventral tegmental area (VTA) and projecting towards the nucleus accumbens (NAc), limbic and cortical areas.

Recent studies suggest that manipulations of key proteins involved in the mesolimbic reward (VTA –NAc) circuit of rodents (e.g. dopamine (DA), CREB, kappa opioid receptor, BDNF) produce unique behavioral phenotypes, some of which may be relevant to depression. I will study genetic variation related to these in association with my ESM momentary assessment paradigm of reward mechanisms in the flow of daily life (see below).

## 2 OBJECTIVES

Primary Objective:

Can the ability to experience positive emotions from everyday life situations assessed with ESM (reward experience), be experimentally modified?

Secondary Objectives:

- ii) Will experimentally induced increases in reward experience in daily life reduce depressive symptoms in patients with residual symptomatology?
- iii) Are polymorphisms of genes coding for key proteins in the mesolimbic reward system associated with reward experience in daily life and acquisition of this ability?

Depressed subjects with (prevalent and harmful) residual symptomatology will be examined. The rationale for this is that examining modification of reward experience in these subjects may additionally shed light on its clinical relevance, i.e. the degree of associated reduction of residual symptoms.

## 3. STUDY DESIGN

### ***Experience Sampling Method***

ESM is a structured diary, momentary assessment technique to study subjects in their daily life. Subjects receive a diary, containing a set of ESM self-assessment forms (rated on 7-point Likert scales) and a digital watch. Ten times a day on six consecutive days, the watch emits a signal at unpredictable moments between 7.30 a.m. and 10.30 p.m. To assess positive affect in responses to environmental situations, reports of current context (activity, persons present, location), rumination, appraisals of the current situation and mood are collected after each “beep”. Previously, I operationalised reward experience as the *effect of minor events on positive affect*. ESM studies individuals prospectively and longitudinally, with short time delays between occurrence and assessment of experiences, minimising biases associated with selective forgetting, attributional style or knowledge about posterior events. I have ample experience with ESM; its validity and feasibility have been extensively documented by our group.

### ***Design***

Subjects are randomised to two groups. At baseline, all subjects will undergo a six-day period of ESM. Then, one group receives MBCT (8 weekly sessions of two hours including daily homework exercises) by an experienced MBCT therapist at the Community Mental Health Centre in Maastricht (CMHC) in addition to care as usual, and the other group only care as usual, followed by a second six-day ESM assessment. Any additional treatment, if applicable, will be kept constant within subjects. Subjects will be globally informed, but remain blind as to how ESM measures relate to testing the hypothesis.

[figure not shown]

\* Subjects are randomized in two groups. The only difference between these two groups is that the experimental group receives 8 weeks of MBCT training and the control group does not. Subjects of both groups continue with care as usual, if any.

## 4. STUDY POPULATION

### 4.1 Population (base)

A sample of 120 depression-remitted subjects with residual symptomatology will be included, recruited from the CMHC in Maastricht, The Netherlands.

### 4.2 Inclusion criteria:

We want to include adult subjects with:

1. a previous episode of major depressive disorder according to DSM-IV criteria
2. residual depressive symptoms: score > 7 on Hamilton Depression Rating Scale (HAM-17), for at least two weeks.

### 4.3 Exclusion criteria

Fulfilling criteria for major depressive disorder according to DSM-IV criteria at the current moment.

### 4.4 Sample size calculation

A power simulation shows that for the least powerful analysis (gene-training effect interaction concerning the polymorphism with the most unequally divided genotypes), the power to detect interaction of small-moderate effect size (0.4) is still 80%. As I will use momentary assessment techniques yielding (6x10x2=) 120 different outcomes within each subject, a relatively small sample is needed for sufficient power to examine power-hungry gene-environment interactions

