### 7.2 Randomisation, blinding and treatment allocation

Subjects are randomized to MBCT + treatment as usual (experimental group) or treatment as usual (control group). Randomization takes place after the baseline measurements and first week of ESM. This is because ESM measurements are not

considered valid in case <30% of the responses are valid. Subjects that have not enough valid ESM response are excluded from the study before randomization. Subjects are obviously not blind to their treatment allocation, however, they do remain blind as to how ESM measures relate to testing the hypothesis.

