### **7.5 Replacement of individual subjects after withdrawal**

In case subjects withdraw before randomization, they will be replaced. After randomization they will not be replaced. The power calculation takes into account a certain amount of drop-out from the study.

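### The 80% power for the gene-by-training interaction in section 4.4 is not supported by the reason given for it, and falls to about 10–20% if 0.4 is an ordinary person-level effect size

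*Protocol*

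**What the plan says.** Section 4.1 fixes the size: "A sample of 120 depression-remitted subjects with residual symptomatology will be included". Section 4.4 gives the only power statement. It begins "A power simulation shows that for the least powerful analysis", identifies that analysis as the "gene-training effect interaction concerning the polymorphism with the most unequally divided genotypes", and concludes that "the power to detect interaction of small-moderate effect size (0.4) is still 80" per cent. The supporting argument follows: "As I will use momentary assessment techniques yielding (6x10x2=) 120 different outcomes within each subject, a relatively small sample is needed".

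Three other places bear on this:

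- Section 7.2 allocates whole persons to arms, and section 9.3 plans a multilevel regression with observations at level 1 and subjects at level 2.
- Section 7.1.1 describes 60 reports per period as a maximum. Section 7.2 excludes persons before randomisation if their diary weeks fall short, because such data are not "considered valid in case <30% of the responses are valid".
- Section 7.5 says that "The power calculation takes into account a certain amount of drop-out from the study" and that subjects lost after randomisation are not replaced. No rate is given.

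The gene-by-training interaction belongs to a secondary objective (sections 2 and 7.1.2). The primary objective, whether training changes reward experience, has no power figure of its own.

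**The concern.** Each person has one genotype and one arm. The interaction contrast compares four genotype-by-arm cells that together hold 120 people. Its precision depends on how much persons differ in their change and on how many persons are in the smallest cells. Repeated reports make each person's own score more exact, but they leave the person-to-person variation in change untouched. Section 4.4 nevertheless offers the number of reports as the reason why a small sample is enough, and says nothing about that variation.

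Two things are at stake. If the true power is far below 80%, a null genetic result could be read as evidence that genotype does not matter. And because the interaction is called the weakest analysis, a reader will assume that the primary comparison has at least 80% power, a figure the protocol never shows.

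**Working it through.** **Inputs from the protocol.** N = 120; effect 0.4 with no unit; power 80%; at most 60 reports per period; at least 30% valid, that is 0.30 × 60 = 18.

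**Assumed, because not stated.** 1:1 allocation (60 per arm), two-sided 5%, two genotype groups with rarer share p, equal variances.

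**The plan's own figure.** The 80% cannot be rebuilt, since the unit of 0.4, the genotype split and the variance components are not given. The results below show how far it depends on them.

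**Reading A: 0.4 is in SDs of person-level change.** The standard error of the interaction contrast is

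SE = SD × √[2/(60p) + 2/(60(1−p))], and power = Φ(0.4/SE − 1.96) + Φ(−0.4/SE − 1.96).

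The effect detectable with 80% power is 2.80 × SE. The N needed for 0.4 is 120 × (detectable effect/0.4)².

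| Split | Persons per cell, each arm | SE (SD = 1) | Power at 0.4 | Effect for 80% | N for 80% at 0.4 |
|---|---|---|---|---|---|
| 50/50 | 30 and 30 | 0.365 | 19.5% | 1.02 SD | 785 |
| 20/80 | 12 and 48 | 0.456 | 14.2% | 1.28 SD | 1226 |
| 10/90 | 6 and 54 | 0.609 | 10.1% | 1.70 SD | 2180 |

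With an assumed 20% loss (48 per arm), power is 16.5%, 12.3% and 9.0%.

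*Primary arm comparison on the same scale.* For 60 v 60 and 0.4 SD, SE = √(2/60) = 0.183 and power is 58% (noncentral t; 59% by the normal approximation). With 48 v 48 it is 49%. The effect for 80% power is 2.80 × √(2/60) = 0.51 SD, or 2.80 × √(2/48) = 0.57 SD with the loss.

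**Reading B: 0.4 is in SDs of single reports.** Let v be the person-by-period variance as a share of total variance. Assume that 0.6 of total variance lies at report level and that 42 of 60 reports (70%) are valid per period. Then

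SD of change = √[2 × (v + 0.6/42)], with 0.6/42 = 0.0143.

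Reaching 80% requires SD of change ≤ 0.4/(2.80 × SE at SD = 1), so v ≤ (that SD)²/2 − 0.0143:

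- 50/50: SD ≤ 0.391, v ≤ 0.062
- 30/70: SD ≤ 0.358, v ≤ 0.050
- 20/80: SD ≤ 0.313, v ≤ 0.035
- 10/90: SD ≤ 0.235, v ≤ 0.013

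Examples that reach 80%: v = 0.05 gives 86% at 50/50 and 80% at 30/70; v = 0.03 gives 84% at 20/80; v = 0.01 gives 85% at 10/90. Examples that do not: v = 0.05 gives 69% at 20/80 and 45% at 10/90; v = 0.15 gives 33% and 21%.

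Reading B treats the outcome as a mean over reports. The endpoint in section 7.1.1 is the effect of positive events on mood, a slope within each person. With few positive events a slope is estimated less precisely than a mean.

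**The case against.** The strongest reply is that 0.4 has no stated unit, so a figure of 10–20% rests on a scale the reviewer has chosen. That stands. Other scales give other answers. As Cohen's f on person-level change, 0.4 gives 99% power, and an f of 0.2 gives 58%. On the single-report scale several combinations pass 80%, as shown above. The genotype splits, the 0.6 share and the 42 reports are also assumptions. A reader might infer from the table that the 80% is simply wrong; the documents do not support that.

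A reader might also infer that the simulation ignored clustering. Nothing shows this. Section 9.3 plans a multilevel model, and treating all 120 × 120 = 14,400 reports as independent would give about 100% for splits from 50/50 to 10/90, not 80%. It is also true that more reports help, in that they reduce within-person error.

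Two further inferences would go too far. Section 7.5 says that drop-out is included, so its absence from section 4.4 is an unreported rate and not a contradiction. The 30% rule is a floor for entry and not an expected response rate.

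What the reply does not rescue is the argument as printed. The number of reports cannot justify a small number of persons unless the between-person variance in change is known to be small, and section 4.4 does not address this. Describing 0.4 as small to moderate is the usual language of a standardised effect, and on that reading, applied to person-level change, the claim fails at every split.

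**Conclusion.** The point holds in this form: the 80% in section 4.4 cannot be reproduced, the reason offered does not support it, and on the ordinary person-level reading power is about 20%, 14% and 10% for splits of 50/50, 20/80 and 10/90. The primary comparison would then have 58%. On the single-report scale, 80% needs a person-by-period variance of at most about 5% of the total at 30/70, 3% at 20/80 and 1% at 10/90. The unequal splits matter most, because the claim is made for the polymorphism with the least balanced genotypes.

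All of these figures rest on 1:1 allocation, a two-sided 5% test and two genotype groups. Those on the single-report scale also need the 0.6 share and 42 valid reports. Because this one number justifies the sample size, it should be corrected or substantiated.

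**What to change.** Keep N = 120 and rewrite section 4.4.

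1. Re-run the simulation with arm and genotype at person level, random event slopes by period, the assumed genotype split, a realistic number of valid reports, and the drop-out that section 7.5 says is included. State the unit of 0.4 along with these inputs.
2. Replace the 80% with the figure that results, and remove the claim that the number of reports makes a small sample sufficient.
3. State power for the primary arm comparison. With 60 v 60, 80% power corresponds to 0.51 SD of person-level change, or 0.57 SD with an assumed 20% loss.
4. Unless the re-run confirms 80%, label the gene-by-training interaction exploratory and give its detectable effect: about 1.0 to 1.7 SD of person-level change for splits from 50/50 to 10/90.

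The cost is a few hours of simulation and probably a less favourable stated power. No further subjects are needed.
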